# 13 Participant timeline

| Activity | Study Period (Days) | | | | |
| --- | --- | --- | --- | --- | --- |
|  | T-1 | T0 | T1 | T2 | T3 |
|  | -7 | 0 | 1-60 (M-F) | 61-70 | 800 |
| **Enrollment** | | | | | |
| Cohort Randomization | x |  |  |  |  |
| Informed Consent |  | x |  |  |  |
| Demographics |  | x |  |  |  |
| Foundational skills survey |  | x |  |  |  |
| **Interventions** | | | | | |
| Distress Thermometer screening |  |  | x |  |  |
| MH&A program |  |  | x |  |  |
| **Assessments** | | | | | |
| TDTP Attendance |  |  | x |  |  |
| TTDP Completion |  |  |  | x |  |
| Employment |  |  |  |  | x |
| Time to Access MH&A |  |  |  | x |  |
| Healthcare utilization |  |  |  | x |  |
| TDTP Satisfaction survey |  |  |  | x |  |
| Case management utilization |  |  |  | x |  |
| Distress Thermometer tool |  |  |  |  |  |
| Acceptability |  |  |  | x |  |
| Feasibility |  |  |  | x |  |
| Compliance |  |  |  | x |  |

# 14 Sample size and power

All power estimations were conducted using nQuery version 8.7.2.0 (<https://www.statsols.com>; accessed June 10, 2022).

## 14.1 Difference in proportion of AFDs

The sample size is fixed at approximately 448 individuals. We anticipate that the first few cohorts will be asked to pilot the screening tool, potentially removing up to 50 apprentices from the final sample size. We will use a fixed sample size of 400 apprentices, divided equally between Sudbury and Barrie sites. The expected cohort sizes will range from 6 to 10 apprentices, resulting in 20 to 34 cohorts per site. We will use a 3-level hierarchical design to model differences in proportion of AFDs where the daily attendance (Level 1) will be coded as binary; 0 for absence and 1 for attendance. Level 1 observations are clustered within individual apprentices (Level 2), which are nested within individual cohorts (Level 3). The sites (Sudbury and Barrie) and start date of cohort enrollment (q1 (January-March); q2 (April-June); q3 (July-Sept); q4 (Oct-Dec) and year) will be included as confounding variables in Level 1 and will not enter into the power calculations. Using this design, we performed a sensitivity analysis to determine the power to observe different primary outcome effect sizes with an $\alpha$-level 0.05**.**  As can be seen in the following table, even small differences in attendance (5% difference in proportions of AFDs) would still be detected with power ≥ 80% as long as the Level 2 inter-cluster correlation ≤ 0.125, a very reasonable assumption as there is no reason to believe that these apprentices’ attendance behaviours will be highly correlated with each other (23).

|  | **Scenarios**^1^ | | | | | | | |
| --- | --- | --- | --- | --- | --- | --- | --- | --- |
| **Variables** | 1 | 2 | 3 | 4 | 5 | 6 | 7 | 8 |
| Test Significance Level, α​ | 0.05 | 0.05 | 0.05 | 0.05 | 0.05 | 0.05 | 0.05 | 0.05 |
| Mean Difference, δ = µ₁ - µ₂​ | 0.1 | 0.15 | 0.05 | 0.05 | 0.05 | 0.05 | 0.05 | 0.1 |
| Standard Deviation, σ​ | 0.1 | 0.1 | 0.1 | 0.1 | 0.1 | 0.1 | 0.15 | 0.15 |
| Level 1 Unit Correlation, ρ₁​ | 0.75 | 0.75 | 0.75 | 0.75 | 0.75 | 0.75 | 0.75 | 0.75 |
| Level 2 Unit Correlation, ρ₂​ | 0.5 | 0.5 | 0.5 | 0.25 | 0.125 | 0.05 | 0.05 | 0.05 |
| Number of Level 3 Units in Group 1, C₁​ | 15 | 15 | 15 | 15 | 15 | 15 | 15 | 15 |
| Number of Level 3 Units in Group 2, C₂​ | 15 | 15 | 15 | 15 | 15 | 15 | 15 | 15 |
| Level 3 Units per Group Ratio, C₂/C₁​ | 1 | 1 | 1 | 1 | 1 | 1 | 1 | 1 |
| Number of Level 2 Units per Level 3 Unit, K​ | 6 | 6 | 6 | 6 | 6 | 6 | 6 | 6 |
| Number of Level 1 Units per Level 2 Unit, M​ | 10 | 10 | 10 | 10 | 10 | 10 | 10 | 10 |
| Power (%)​ | 95.9 | 99 | 45.7 | 65.4 | 80.9 | 91.1 | 59.8 | 99 |

^1^ Highlighted cells (Yellow) represent changes from previous scenario

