## 14.2 Difference in proportions of TDTP completion

Historical cohorts have demonstrated variation in program completion proportions but have been generally observed at a 75-80% graduation / completion rate. In this cluster randomized trial comparing the difference in proportions of TDTP completion, we define an *a priori* difference of ≥ 0.1 in completion proportions as the lower limit of a minimally significant difference (24). This is opinion-based on an informal survey of TDTP stakeholders. Given the same fixed sample and cohort size estimates discussed in Section 14.1, we performed a sensitivity analysis to determine the power to observe a difference in program completion proportions ≥ 0.1 using different control group completion rates with an $\alpha$-level 0.05**.**  As can be seen in the following table, a difference in completion proportions of 0.1 would be detected with power ≥ 80% as long as the control group completion proportion was ≥ 0.8, a reasonable assumption given the historically observed program completion proportions.

|  | **Scenarios**^1^ | | | | | | |
| --- | --- | --- | --- | --- | --- | --- | --- |
| **Variables** | 1 | 2 | 3 | 4 | 5 | 6 | 7 |
| Test Significance Level, α​ | 0.05 | 0.05 | 0.05 | 0.05 | 0.05 | 0.05 | 0.05 |
| 1 or 2-Sided Test?​ | Two | Two | Two | Two | Two | Two | Two |
| Control Group Proportion (p2)​ | 0.75 | 0.75 | 0.75 | 0.75 | 0.8 | 0.8 | 0.8 |
| Test Statistic under H0​ | 0 | 0 | 0 | 0 | 0 | 0 | 0 |
| Test Statistic under H1​ | 0.1 | 0.1 | 0.1 | 0.1 | 0.1 | 0.1 | 0.1 |
| Intracluster Correlation (ICC)​ | 0 | 0.05 | 0 | 0 | 0 | 0 | 0 |
| Clusters in Treatment Group (K1)​ | 20 | 20 | 33 | 25 | 20 | 33 | 25 |
| Clusters in Control Group (K2)​ | 20 | 20 | 33 | 25 | 20 | 33 | 25 |
| Cluster Ratio (K2/K1)​ | 1 | 1 | 1 | 1 | 1 | 1 | 1 |
| Cluster Sample Size in Treatment Group (M1)​ | 10 | 10 | 6 | 8 | 10 | 6 | 8 |
| Cluster Sample Size in Control Group (M2)​ | 10 | 10 | 6 | 8 | 10 | 6 | 8 |
| Cluster Sample Size Ratio (M2/M1)​ | 1 | 1 | 1 | 1 | 1 | 1 | 1 |
| Power (%)​ | 70.6 | 54.6 | 70.2 | 70.6 | 80.2 | 79.8 | 80.2 |

^1^ Highlighted cells (Yellow) represent changes from previous scenario

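### The Section 14.1 attendance power rests on a standard deviation (0.1) that a 0/1 daily outcome cannot have, so the 80% power claim for a 5-point difference is unsupported

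*Protocol*

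**What the plan says.** Section 14.1 describes a three-level model for absence-free days (AFDs), "where the daily attendance (Level 1) will be coded as binary; 0 for absence and 1 for attendance", with days nested in apprentices and apprentices in cohorts. The power table treats the comparison as a difference in means. Its standard deviation row reads "0.1 | 0.1 | 0.1 | 0.1 | 0.1 | 0.1 | 0.15 | 0.15". The number of Level 1 units per apprentice is "10 | 10 | 10 | 10 | 10 | 10 | 10 | 10". The Level 1 correlation is 0.75 throughout, the Level 2 correlation runs from 0.5 down to 0.05, and each group has 15 cohorts of 6.

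From scenarios 5 and 6 (stated power 80.9% and 91.1%) the text concludes that "even small differences in attendance (5% difference in proportions of AFDs) would still be detected with power ≥ 80% as long as" the Level 2 correlation does not exceed 0.125. No source is given for the SD. No expected attendance rate appears anywhere in the protocol. The nearest historical figure is for completion, in Section 14.2: past cohorts "have been generally observed at a 75-80% graduation / completion rate".

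**The concern.** In a three-level comparison of means, sigma is the SD of one Level 1 observation. Here that observation is a single day scored 0 or 1, whose SD is fixed by its mean. An SD of 0.1 is much smaller than a binary day can have at any ordinary attendance level, and power is very sensitive to it.

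Attendance is one of three primary outcomes, and the protocol tells its readers that even small effects on it will be found. If that is untrue, a null attendance result could be read as evidence of no effect when the trial had little chance of showing one.

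**Working it through.** **Inputs from Section 14.1.** delta = 0.05; sigma = 0.1; rho1 = 0.75; rho2 = 0.125 (scenario 5) or 0.05 (scenario 6); C = 15 cohorts per group; K = 6 apprentices per cohort; M = 10 days per apprentice; alpha = 0.05. Section 14.1 does not state sidedness. Section 14.2 is two-sided ("Two | Two | Two | Two | Two | Two | Two"), and two-sided reproduces the 14.1 figures.

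**Formula.** Design effect f = 1 + (M-1)rho1 + M(K-1)rho2; effective n per arm = CKM/f; SE = sigma × sqrt(2/n_eff); power = Φ(delta/SE - 1.96), ignoring the opposite tail.

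**Reproducing the plan (scenario 5).** f = 1 + 9×0.75 + 10×5×0.125 = 14.0. n_eff = 900/14.0 = 64.3. SE = 0.1 × sqrt(2/64.3) = 0.0176. Power = Φ(2.835 - 1.96) = 80.9%, as stated. All eight scenarios:

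| Scenario | 1 | 2 | 3 | 4 | 5 | 6 | 7 | 8 |
|---|---|---|---|---|---|---|---|---|
| Stated % | 95.9 | 99 | 45.7 | 65.4 | 80.9 | 91.1 | 59.8 | 99 |
| Recomputed % | 96.0 | 100 | 45.8 | 65.4 | 80.9 | 91.2 | 59.8 | 99.3 |

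A one-sided test (88.3% for scenario 5) or a t-test on 28 df (78.1%) does not match. The formula is therefore identified, and sigma in it is the SD of one day.

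**Checking sigma.** For a 0/1 variable, SD = sqrt(p(1-p)). Setting this to 0.1 gives p = 0.990; setting it to 0.15 gives p = 0.977. From either, a 5-point rise would pass 100%.

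**Replacing sigma.** Use the SD averaged over the two arms. For 85% against 90%: sqrt((0.1275 + 0.0900)/2) = 0.330. In scenario 5, SE = 0.330 × sqrt(2/64.3) = 0.0582, and power = Φ(0.860 - 1.96) = 13.6%.

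Control attendance below is an assumption. Each cell gives power (%) for 5 points at rho2 = 0.125 / 0.05, with rho1 = 0.75.

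| Control to intervention | SD | Table layout: 15×6, 10 days | Pooled: 33×6 per arm, 48 days | Pooled: 20×10 per arm, 48 days |
|---|---|---|---|---|
| 75 to 80% | 0.417 | 10.0 / 12.2 | 17.3 / 22.1 | 13.9 / 19.3 |
| 80 to 85% | 0.379 | 11.3 / 13.9 | 20.0 / 25.7 | 15.9 / 22.4 |
| 85 to 90% | 0.330 | 13.6 / 17.0 | 25.0 / 32.4 | 19.6 / 28.1 |
| 90 to 95% | 0.262 | 19.0 / 24.3 | 36.5 / 47.3 | 28.5 / 41.2 |

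The stated values for the same two correlations are 80.9 / 91.1. Using 10 days rather than the 48 of Section 12.11 hardly matters at rho1 = 0.75: for 85 to 90% with 33×6, power is 24.7% with 10 days and 25.0% with 48.

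**Sensitivity to rho1.** At rho1 = 0.25 and control attendance 80-90%, power is about 15-39% in the table's layout. With 33×6 and 48 days it is at most 75% (90 to 95%, rho2 = 0.05).

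**Detectable difference at 80% power** (rho1 = 0.75, 48 days, rho2 0.125 to 0.05, control 0.80-0.85). All 400 pooled (33×6 or 20×10 per arm): about 9-13 points. One site only (17×6 or 10×10 per arm): about 11-17 points.

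**The case against.** **Sigma might be a person-level SD.** If 0.1 meant the SD of each apprentice's AFD proportion, n_eff = CK/(1 + (K-1)rho2), and the table's layout would give about 75% (rho2 0.125) to 85% (rho2 0.05). The table itself argues against this reading, because it applies sigma together with M = 10 and rho1 = 0.75. With those values, binary days imply a person-level SD of sqrt(p(1-p)(1 + 9×0.75)/10), which is 0.31 at 85% attendance and 0.26 at 90%. An independent guess gives a similar picture. Suppose 20-25% drop out and attend 25-50% of days, against 90-95% for completers (attendance figures assumed). The split alone then gives an SD between sqrt(0.20×0.80)×0.40 = 0.16 and sqrt(0.25×0.75)×0.70 = 0.30. What stands is that the claim fares better here: at SD 0.16 with 33×6 per arm, power is about 68-79%, and at SD 0.15 about 74-84%. A person-level SD from past records could therefore move the answer appreciably.

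**Attendance might be near the ceiling.** At 94 to 99%, power is 34-44% in the table's layout and about 52-78% pooled. It passes 80% only near 95 to 100% with all 400 pooled and rho2 = 0.05. This is hard to square with 75-80% completion: AFDs count every program day the apprentice is alive, so if 20% drop out and attend at most half the days, mean attendance cannot exceed 0.80 + 0.20×0.50 = 90%. Late leavers could attend more, so this is an argument and not a proof.

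**A reader might infer that 180 people is an error against the planned 400.** The documents do not show that. ICM10 against BCM is a contrast within Sudbury, with about 200 apprentices and 20 to 34 cohorts, or 10 to 17 per arm; 15 cohorts of 6 per group fits it. Section 14.1 does not say which contrast it powers.

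**The sample size is fixed by funding, and the table is a sensitivity analysis.** True: the correction changes no recruitment or analysis. It changes what the protocol may claim.

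**Conclusion.** The claim is wrong as written. The calculation is correct for its inputs, but an SD of 0.1 or 0.15 is incompatible with a 0/1 Level 1 outcome that is to rise by 5 points, so power of at least 80% for that difference is not shown.

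With rho1 = 0.75, rho2 = 0.125 to 0.05 and assumed control attendance of 75-90%, power is about 10-24% in the table's layout and about 14-47% with all 400 pooled and 48 days. Lowering rho1 to 0.25 still leaves it at or below about 75% for control attendance of 80-90%.

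A reader might want one figure for the true power, or one detectable difference. The documents support neither: both depend on an attendance rate that the protocol never gives, on an unsourced rho1, and on whether the contrast is pooled or within one site.

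**What to change.** In Section 14.1:

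- Delete the sentence claiming at least 80% power for a 5-point difference.
- State which contrast is powered (the pooled tool effect, or ICM10 against BCM within one site) and its cohort numbers.
- Recompute the table with sqrt(p(1-p)) over a stated range of control attendance, or with a person-level SD taken from past training-program attendance records. Use 48 days and a range of rho1 and rho2.
- Report power and the detectable difference as ranges with their assumptions. On those used here (rho1 = 0.75, control attendance 0.80-0.85), the detectable difference at 80% power is about 9-13 points with all 400 pooled and about 11-17 points for a single-site contrast.

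The cost is one rewritten paragraph and table, and a less favourable stated power. No participants are added.

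### Section 14.1 ties 80% power for a 5-point attendance difference to the Level 2 correlation alone, but its table supports this only at SD 0.1; scenario 7 meets the stated condition and gives 59.8%

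*Protocol*

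**What the plan says.** Protocol Section 14.1 concerns the attendance outcome, listed first among the primary outcomes in Section 12.1. It fixes the sample at 400 apprentices, describes a three-level model (days within apprentices within cohorts), and presents eight power scenarios as a sensitivity analysis. The text above the table then sums up: a 5-point difference "would still be detected with power ≥ 80% as long as the Level 2 inter-cluster correlation ≤ 0.125". It goes on to defend the correlation as reasonable and says nothing about the SD.

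The relevant table rows, scenarios 1 to 8 in order, are:

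- mean difference: "0.1 | 0.15 | 0.05 | 0.05 | 0.05 | 0.05 | 0.05 | 0.1"
- SD: "0.1 | 0.1 | 0.1 | 0.1 | 0.1 | 0.1 | 0.15 | 0.15"
- Level 2 correlation: "0.5 | 0.5 | 0.5 | 0.25 | 0.125 | 0.05 | 0.05 | 0.05"
- power (%): "95.9 | 99 | 45.7 | 65.4 | 80.9 | 91.1 | 59.8 | 99"

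Every scenario has alpha 0.05, Level 1 correlation 0.75, 15 cohorts per group, 6 apprentices per cohort and 10 days per apprentice.

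**The concern.** The sentence offers an upper limit on the Level 2 correlation as a sufficient condition for 80% power and cites the table as proof. One column of that table satisfies the condition and falls about 20 points short. The missing element is the SD, which the plan itself varies between 0.1 and 0.15. The protocol gives no source for either value and does not name one as the base case.

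At stake is how a reader judges the attendance outcome. Someone who relies on the text would conclude that only a high correlation between apprentices of the same cohort could threaten power for a 5-point effect, and might later read a null attendance result as evidence against an effect of that size. At the plan's own second SD value, that confidence is not warranted for the layout shown.

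**Working it through.** **Inputs**, all from the table in Section 14.1: difference δ; SD σ; ρ1 = 0.75; ρ2 as listed; C = 15 cohorts per group; K = 6 apprentices per cohort; M = 10 days per apprentice; α = 0.05. The table does not say whether the test is one- or two-sided. Two-sided reproduces it; one-sided does not (scenario 7 would be 71.4%).

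**Formulas.** Design effect DE = 1 + (M − 1)ρ1 + M(K − 1)ρ2 = 7.75 + 50ρ2. Standard error of the difference SE = σ√(2·DE / CKM), with CKM = 900. Power = Φ(δ/SE − 1.96).

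**Reproducing the table**

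| Scenario | δ | σ | ρ2 | DE | Computed power (%) | Stated power (%) |
|---|---|---|---|---|---|---|
| 1 | 0.10 | 0.10 | 0.5 | 32.75 | 96.0 | 95.9 |
| 2 | 0.15 | 0.10 | 0.5 | 32.75 | 99.98 | 99 |
| 3 | 0.05 | 0.10 | 0.5 | 32.75 | 45.8 | 45.7 |
| 4 | 0.05 | 0.10 | 0.25 | 20.25 | 65.4 | 65.4 |
| 5 | 0.05 | 0.10 | 0.125 | 14.00 | 80.9 | 80.9 |
| 6 | 0.05 | 0.10 | 0.05 | 10.25 | 91.2 | 91.1 |
| 7 | 0.05 | 0.15 | 0.05 | 10.25 | 59.8 | 59.8 |
| 8 | 0.10 | 0.15 | 0.05 | 10.25 | 99.3 | 99 |

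Scenarios 1 and 3 to 7 agree within 0.1 point, and 2 and 8 within one point. The table entries can be trusted.

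**Testing the sentence against the table.** Its condition is δ = 0.05 and ρ2 ≤ 0.125. Scenarios 5, 6 and 7 meet it. Scenarios 5 and 6 reach 80%; scenario 7 does not. Scenarios 6 and 7 differ only in the SD:

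- Scenario 6: SE = 0.10 × √(20.5/900) = 0.0151; 0.05/SE = 3.313; power = Φ(1.353) = 91.2%.
- Scenario 7: SE = 0.15 × √(20.5/900) = 0.0226; 0.05/SE = 2.209; power = Φ(0.249) = 59.8%.

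**How much room the SD has, in this layout.** The largest SD giving 80% power for δ = 0.05 is 0.05 / [(1.960 + 0.842)√(2·DE/900)]. The difference detectable with 80% power at SD 0.15 is 0.15 × 2.802 × √(2·DE/900).

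| ρ2 | Largest SD for 80% power | Power at SD 0.15 (%) | Detectable difference at SD 0.15 |
|---|---|---|---|
| 0 | 0.136 | 71.9 | 0.055 |
| 0.05 | 0.118 | 59.8 | 0.063 |
| 0.125 | 0.101 | 47.2 | 0.074 |

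**Other layouts.** Section 14.1 also speaks of 400 apprentices in 20 to 34 cohorts per site, whereas the table's layout has 2 × 15 × 6 = 180 apprentices. If a comparison had about 200 apprentices per group, the same formula at SD 0.15 with 10 days gives:

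| Cohorts × size per group | Power at ρ2 = 0.05 (%) | Power at ρ2 = 0.125 (%) |
|---|---|---|
| 33 × 6 | 90.6 | 80.0 |
| 25 × 8 | 88.2 | 73.7 |
| 20 × 10 | 85.4 | 67.7 |

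The comparisons between single factorial cells in Section 7.1 have about 100 per group (400/4). With 17 cohorts of 6 and the full 48 days of Section 12.11, power at SD 0.15 and ρ2 = 0.05 is 66.1%.

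**The case against.** The best defence is that the sentence summarises scenarios 3 to 6, which hold the difference at 0.05 and the SD at 0.1 and vary only the Level 2 correlation. Read that way it is accurate: power crosses 80% at 0.125. Scenarios 7 and 8 then explore a different SD, and the 59.8% is printed directly below, so nothing is hidden. The sample is also fixed by programme funding (Section 1.1), so no sample size was derived from this sentence.

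Most of this stands. The fault is a missing qualifier, not a calculation error, and the consequence is for interpretation, not enrolment. But the sentence does not confine itself to SD 0.1; it points to the table as a whole, and the table contains a case that contradicts it.

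A reader might go further and infer that SD 0.15 removes 80% power at every correlation, so that the trial cannot detect a 5-point difference. The document does not support that as a general statement. It is true of 15 cohorts of 6 with 10 days, where even zero correlation gives only 71.9%. With about 200 apprentices per group, power at SD 0.15 reaches 85.4% to 90.6% at a correlation of 0.05. Nor do the larger layouts rescue the sentence: it rests on the table, and with 20 cohorts of 10 the power at a correlation of 0.125 is still 67.7%.

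**Conclusion.** The point holds in a limited form. As written, the summary sentence in Section 14.1 is contradicted by scenario 7 of its own table, which gives 59.8% where the text promises at least 80%. The sentence is correct if restricted to SD 0.1, with little margin at a correlation of 0.125 (80.9%; SD no larger than about 0.101). The contradiction itself rests on no assumption beyond the printed table. The supplementary figures assume a two-sided normal test and, except where another layout is named, the table's 15 cohorts of 6 per group with 10 days. No conclusion follows about which SD is right for this outcome, since the protocol gives no basis for choosing, or about the power of the trial as a whole.

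**What to change.** Replace the summary sentence in Section 14.1 with one that matches the table, for example: *With 15 cohorts of 6 apprentices per group and 10 days per apprentice, power for a 5% difference is at least 80% for a Level 2 correlation of 0.125 or less if the SD is 0.1 (scenarios 5 and 6); at SD 0.15 it is 59.8% at a correlation of 0.05 (scenario 7).*

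If a detectable difference at SD 0.15 is added, give it for this layout only: about 0.055, 0.063 and 0.074 at correlations of 0, 0.05 and 0.125. A short note on where the SD values come from would help.

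The cost is one reworded sentence and a less favourable stated power. Design, enrolment, conduct and analysis do not change.

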## 14.2 Difference in proportions of TDTP completion

Historical cohorts have demonstrated variation in program completion proportions but have been generally observed at a 75-80% graduation / completion rate. In this cluster randomized trial comparing the difference in proportions of TDTP completion, we define an *a priori* difference of ≥ 0.1 in completion proportions as the lower limit of a minimally significant difference (24). This is opinion-based on an informal survey of TDTP stakeholders. Given the same fixed sample and cohort size estimates discussed in Section 14.1, we performed a sensitivity analysis to determine the power to observe a difference in program completion proportions ≥ 0.1 using different control group completion rates with an $\alpha$-level 0.05**.**  As can be seen in the following table, a difference in completion proportions of 0.1 would be detected with power ≥ 80% as long as the control group completion proportion was ≥ 0.8, a reasonable assumption given the historically observed program completion proportions.

|  | **Scenarios**^1^ | | | | | | |
| --- | --- | --- | --- | --- | --- | --- | --- |
| **Variables** | 1 | 2 | 3 | 4 | 5 | 6 | 7 |
| Test Significance Level, α​ | 0.05 | 0.05 | 0.05 | 0.05 | 0.05 | 0.05 | 0.05 |
| 1 or 2-Sided Test?​ | Two | Two | Two | Two | Two | Two | Two |
| Control Group Proportion (p2)​ | 0.75 | 0.75 | 0.75 | 0.75 | 0.8 | 0.8 | 0.8 |
| Test Statistic under H0​ | 0 | 0 | 0 | 0 | 0 | 0 | 0 |
| Test Statistic under H1​ | 0.1 | 0.1 | 0.1 | 0.1 | 0.1 | 0.1 | 0.1 |
| Intracluster Correlation (ICC)​ | 0 | 0.05 | 0 | 0 | 0 | 0 | 0 |
| Clusters in Treatment Group (K1)​ | 20 | 20 | 33 | 25 | 20 | 33 | 25 |
| Clusters in Control Group (K2)​ | 20 | 20 | 33 | 25 | 20 | 33 | 25 |
| Cluster Ratio (K2/K1)​ | 1 | 1 | 1 | 1 | 1 | 1 | 1 |
| Cluster Sample Size in Treatment Group (M1)​ | 10 | 10 | 6 | 8 | 10 | 6 | 8 |
| Cluster Sample Size in Control Group (M2)​ | 10 | 10 | 6 | 8 | 10 | 6 | 8 |
| Cluster Sample Size Ratio (M2/M1)​ | 1 | 1 | 1 | 1 | 1 | 1 | 1 |
| Power (%)​ | 70.6 | 54.6 | 70.2 | 70.6 | 80.2 | 79.8 | 80.2 |

^1^ Highlighted cells (Yellow) represent changes from previous scenario

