### 5.15 Trades & Diversity Training Program (TDTP)

The TDTP is a federally-funded vocational construction skills training program. TDTP is funded through the Government of Canada’s Skilled Trades Awareness and Readiness Program initiative (15), which focuses on helping individuals who face barriers to employment to develop skills and experience they need to find a job or continue their education. The TDTP has been developed and will be delivered by Community Builders®, a social enterprise located in Minesing, Ontario, Canada (<https://www.communitybuilders.co/community-impact/training-and-employment/>). The TDTP is not part of a formal education program and does not lead to formal Red Seal certification for any of the construction trades. As part of the TDTP, Community Builders® provides a Case Manager for each cohort who regularly interacts with each apprentice to help them navigate external services and supports for any barriers that may exist or arise during training that threaten their ongoing participation or completion. TDTP is a cohort-based construction skills training program, with anticipated class sizes between 8 and 15 participants. Each cohort will experience structured activities over a 12-week period that include both in-classroom education and supervised hands-on experiential learning at participating construction sites. The in-class component will account for 22% (102 total hours) of the 12-week program. The in-class component will be led by the Construction Trainer, Case Manager, and Program Director. The in-class component will focus on teaching life skills needed for employment, referred to as the socio-economic & construction curriculum. The curriculum will include lessons about, but not be limited to the following: trade-specific vocabulary; trade math skills; ways to effective communication; conflict resolution in the workplace (referred to as soft skills); health and safety in the workplace; career / trade exploration; and interview and resumé-writing skills. The remaining 78% (360 total hours) will be spent on-site in supervised, hands-on learning. TDTP will target visible minorities, individuals who are Indigenous, and women for enrollment.

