# 6 Hypotheses

## 6.1 Primary

In apprentices enrolled in the TDTP who are at-risk of absenteeism, drop-out or unemployment post-program completion, exposure to either the ICM^10^ or ICM^01^ models will be superior to the BCM model for reducing absenteeism (as determined by the number of absence-free days), drop-out (as determined by the proportion of apprentices completing the program), and unemployment (as determined by proportion employed at 24 months post-program completion).

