# 20 Statistical methods

## 20.1 Outcomes

The intervention arms (ICM^10^ (Distress Thermometer screening tool), ICM^01^ (MH&A fit-for-purpose program), ICM^11^ (Both Distress Thermometer and MH&A) will be compared against the active comparator (BCM) for all primary and secondary analyses where applicable. All inferential and descriptive analyses will be at the individual level after accounting for the effects of clustering (id and cohort).

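### The ≥80% power for program completion in Section 14.2 assumes no clustering and 200 per arm, while the stated hypotheses compare cells of about 100 in a cluster-randomised trial

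*Protocol*

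**What the plan says.** Section 14.2 of the Protocol presents seven power scenarios for a 0.10 difference in completion. It concludes that "a difference in completion proportions of 0.1 would be detected with power ≥ 80% as long as the control group completion proportion" is at least 0.8, and calls this reasonable because past completion was "generally observed at a 75-80% graduation / completion rate".

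The supporting scenarios are 5 to 7, with control 0.80, ICC 0 and powers of 80.2, 79.8 and 80.2%. The only scenario with clustering is number 2 (ICC 0.05, control 0.75), which shows 54.6%.

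The comparisons are defined elsewhere:
- Section 6.1 hypothesises that "exposure to either the ICM^10^ or ICM^01^ models will be superior to the BCM model", and Section 7.1 builds its objectives on the same cells.
- Section 5.3 names BCM as the control for each of those two models.
- Section 20.1 says the three intervention arms "will be compared against the active comparator (BCM) for all primary and secondary analyses where applicable".

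Cohort size is given twice: 6 to 10 in Section 14.1, and in Section 5.15 the program is described "with anticipated class sizes between 8 and 15 participants". Section 14.3 has no calculation of its own and refers back to the completion result.

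**The concern.** Setting the ICC to 0 turns a cluster-randomised calculation into an individually randomised one. No scenario combines control 0.80 with any clustering, yet the conclusion is drawn for the cluster trial. In addition, 200 per arm is the size of the pooled tool versus no-tool comparison, not of a cell compared with BCM. Section 14.1 itself uses 15 cohorts of 6 per group (90 against 90), which is cell-sized, while Section 14.2 says it keeps the same sample and cohort assumptions but has about twice as many per arm.

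Program completion is a primary outcome. If a reader believes the trial had 80% power for a 10-point gain, a null cell comparison will be taken as evidence against that gain when the design had a much smaller chance of showing it.

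**Working it through.** **Inputs**
- Alpha: "0.05 | 0.05 | 0.05 | 0.05 | 0.05 | 0.05 | 0.05"; sidedness: "Two | Two | Two | Two | Two | Two | Two" (14.2 table).
- Control completion by scenario: "0.75 | 0.75 | 0.75 | 0.75 | 0.8 | 0.8 | 0.8"; difference 0.10 throughout.
- Per arm: 20×10 = 200, 33×6 = 198, 25×8 = 200 (14.2 table).
- Cell size: 400 split equally over two sites (14.1) gives 200 per site; 1:1 allocation to the tool within site (Section 8) gives about 100 per cell.
- Cohort size m: 6 to 10 (14.1).
- ICC: 0 or 0.05 (14.2 table); 0.01–0.10 is my assumed range.

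**Formula**

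n_eff = n / [1 + (m − 1)·ICC], with p̄ = (p1 + p2)/2.

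SE0 = √[2p̄(1 − p̄)/n_eff] and SE1 = √{[p1(1 − p1) + p2(1 − p2)]/n_eff}.

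Power = Φ[(0.10 − 1.96·SE0)/SE1].

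**Step 1: reproduce the table.** Scenario 5 (0.80 v 0.90, n = 200, ICC 0): SE0 = 0.0357, SE1 = 0.0354, z = (0.10 − 0.0700)/0.0354 = 0.849, power 80.2%. All seven scenarios give 70.7, 54.7, 70.3, 70.7, 80.2, 79.8 and 80.2%, against the stated 70.6, 54.6, 70.2, 70.6, 80.2, 79.8 and 80.2%. The method is therefore the protocol's own to within 0.1 point.

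**Step 2: change only the contrast.** Control 0.80, n = 100, ICC 0: SE0 = 0.0505, SE1 = 0.0500, z = (0.10 − 0.0990)/0.0500 = 0.02, power 50.8%. At control 0.75 it is 42.3%.

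**Step 3: add ICC 0.05.** For m = 10 the design effect is 1 + 9×0.05 = 1.45, so 100 becomes 69.0 effective. Then SE0 = 0.0608, SE1 = 0.0602, z = −0.319 and power is 37.5%.

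| Power (%) at ICC 0.05 | m = 6 | m = 8 | m = 10 |
|---|---|---|---|
| Design effect | 1.25 | 1.35 | 1.45 |
| Cell, 100 v 100, control 0.80 | 42.4 | 39.8 | 37.5 |
| Tool main effect, 200 v 200, control 0.80 | 70.9 | 67.5 | 64.4 |
| Cell, control 0.75 | 35.1 | 32.9 | 31.0 |
| Tool main effect, control 0.75 | 61.0 | 57.7 | 54.7 |

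**Step 4: vary the ICC** (control 0.80, m = 6 to 10)

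| ICC | Cell, % | Tool main effect, % |
|---|---|---|
| 0.01 | 47.5–48.9 | 76.7–78.3 |
| 0.02 | 44.5–47.1 | 73.4–76.3 |
| 0.05 | 37.5–42.4 | 64.4–70.9 |
| 0.10 | 29.9–36.4 | 52.9–62.9 |

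**Step 5: the other cohort size.** With cohorts of 15, the top of the range in Section 5.15, ICC 0.05 and control 0.80 give 32.8% (cell) and 57.5% (main effect).

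**The case against.** **The arithmetic is sound and nothing is hidden.** Every power in the table reproduces, and the table prints the 54.6% scenario. The sample is fixed by program funding (Section 1.1), so the power claim did not set its size. This stands. The faults are in the assumptions, the contrast and the concluding sentence. The only numerical slip is 79.8% counted as at least 80%.

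**The tool main effect can be estimated.** The factorial model in 20.11b, followed by marginal estimates, could deliver a 200 against 200 comparison. That is fair, but Sections 6.1 and 5.3 name cell comparisons with BCM. Even the main effect falls below 80% at ICC 0.01.

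**The ICC is not known.** This also stands. A reader might take 38–42% as the trial's actual power, but it holds only at ICC 0.05, control 0.80 and cohorts of 6–10. Nor can the correlations in Section 14.1 supply a completion ICC. They concern daily attendance, and 0.125 appears there as an upper tolerance.

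**Cohorts of 15 are not established.** Section 5.15 describes class sizes. Study participation is voluntary (Section 15), so the study cohorts could be smaller. The two passages need reconciling, and the main result above does not depend on the larger size.

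**Further inferences the documents do not support.** A reader might go on to ask for one primary contrast, a fixed testing order, or a family-wise error figure. The number of tests depends on which section is counted, multiplicity may be handled in an SAP that is not shown, and nothing in the protocol ranks completion first among the three primary outcomes.

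**Conclusion.** The point holds. The sentence claiming at least 80% power describes an unclustered 200 against 200 comparison, which is neither the design nor the stated primary hypothesis.

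With control completion at 0.80, no ICC brings the cell contrast above about 51%. At ICC 0.05 and cohorts of 6–10 it has about 38–42%, and the tool main effect about 64–71%. At control 0.75, the lower end of the protocol's own history, the figures are about 31–35% and 55–61%. Over ICC 0.01–0.10 at control 0.80, the cell contrast has about 30–49% and the main effect about 53–78%.

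These values assume equal cohort sizes, four cells of about 100, a normal approximation and no loss from the additional model terms in 20.11b. The conclusion that 80% is not supported holds at every non-zero ICC examined. The exact power depends on an ICC that the protocol does not establish.

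**What to change.** - In Section 14.2, replace the concluding sentence and the table with power for each contrast the protocol states: cell against BCM (about 100 v 100) and the tool main effect (200 v 200). Label every figure with its contrast.
- Use a non-zero ICC, for example 0.01–0.10, with control completion 0.75–0.80.
- Reconcile the cohort size between Section 5.15 (8–15) and Section 14.1 (6–10), and use the agreed range.
- Correct Section 14.3, which relies on 14.2. Section 12.13 counts graduates only, so a cell of 100 with 75–80% completion leaves about 75–80 for the employment analysis.

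The cost is one recalculated table and revised text in two or three sections. The stated power becomes less favourable. No participants are added, and the hypotheses and primary outcomes can stay as they are.
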